**4. Settings**

| Institutions | No. Of participants to recruit |
| --- | --- |
| Nanjing Drum Tower Hospital (leader institution) | 296 |
| Wuxi Maternal and Child Health Hospital | 52 |
| Taixing People's Hospital | 52 |
| The First People's Hospital of Kunshan | 52 |
| Jintan People's Hospital | 52 |

**5. Funding**

Funding for this study is provided by National Key Clinical Department of Ministry of Health of China (2011271).

**6. Implementation of the trial**

1. **Implementation methods of Foley catheter balloon induction**

**A. Recruitment and consent**

After admission for term labor induction, women will be evaluated for indications and contraindications for induction by the obstetricians. Gestational age will be confirmed and the status of the cervix will be determined by the Bishop pelvic scoring system [8]. Vaginal discharge will be tested to exclude vaginal infection. Ultrasound results will be reviewed to exclude placenta previa. Potential participants will be informed about the trial and given information when the decision to induce labor is made after admission. Those women who wish to participate and who understand the nature of the trial will be asked to complete and sign two copies of the consent form. If woman dose not wish to participant in the trial, she will receive other method of induction according to each hospital’s protocol.

**B. Randomization**

After informed consent, the obstetrician and another investigator will open the envelope containing the assignment information. At enrollment, the obstetricians will record medical history and indications for induction in *Induction of Labor Checklist* (Appendix 1.).

**C. Interventions** **Protocol for Foley catheter insertion.** The cervix will be exposed with a sterile speculum and cleansed with a povidone-iodine solution. Under direct visualization, a 16-F Foley catheter will be inserted into the endocervical canal. Once the catheter is past the internal os, the catheter balloon will be inflated with sterile saline solution and pulled against the internal os of the cervix. The external end of Foley catheter will be taped with tension to the medial aspect of the woman’s thigh. Non-stress test will be conducted after catheter insertion. Women in group 1 and group 2 will have a 30ml Foley catheter balloon, with a maximum ripening time of 12 hours and 24 hours respectively. Women in group 3 and group 4 will have an 80ml balloon with a maximum of 12 hours and 24 hours exposure respectively.

The following will be indications for early cessation of treatment: (1) failure to insert the Foley catheter ; (2) severe bleeding or discomfort after insertion; (3) either participants or the supervising obstetricians call for the cessation of the trial. The obstetrician will be informed and still collect outcome data from women who have stopped treatments.

In all groups, the Foley catheter will be removed for the following reasons: (1) the time limitation for ripening is reached; (2) spontaneous rupture of membranes has occurred; (3) the balloon is expelled spontaneously; (4) women enter the active phase of labor; or (5) hyperstimulation or fetal distress is suspected.

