**3. Study Design**

1. **Study Design** It is an open-label, randomized, controlled trial in a multi-center setting. Participants will be randomly allocated to one of four parallel groups, in 1:1:1:1 ratio, to receive either one of four treatments: (1) 30 mL balloon for a maximum of 12 hours, (2) 30 mL balloon for a maximum of 24 hours, (3) 80 mL balloon for a maximum of 12 hours, (4) 80 mL balloon for a maximum of 24 hours. Neither the investigator nor the participants are blind to the assignment.
2. **Randomization** The randomization sequence is computer-generated with variable blocks in 1:1:1:1 allocation for each arm by the statistician ([name]). Since 95% of women undergoing labor induction in our district are nulliparous, we will not stratify women according to parity. The randomization sequence will be placed into numbered opaque envelopes by two doctors uninvolved in the trial before the initiation of the study. None of the clinical investigators will have access to the schedule until completion of the study.
3. **Inclusion /Exclusion Criteria** Women scheduled for labor induction will be screened for eligibility. Inclusion criteria are gestational age ≥ 37 weeks; singleton gestation with cephalic presentation; intact membranes; reactive non-stress test and Bishop’s score < 6. Women less than 18 years, with multiple pregnancy, abnormal pelvimetry, abnormal presentation, placenta previa, vaginal infection, intrauterine fetal death, or GBS positive will be excluded.
4. **Primary Outcome** The primary outcome is vaginal delivery within 24 hours.
5. **Secondary outcomes** Secondary maternal outcomes are cesarean section rate, instrumental vaginal delivery, indications for operative delivery, induction-to-delivery time, induction-to-active phase time, epidural analgesia, oxytocin use, uterine hyperstimulation, chorioamnionitis, postpartum hemorrhage (blood loss >500ml within 24h after delivery)，postpartum transfusion, cervical dilation and station. Secondary neonatal outcomes include birth weight, the rate of Apgar scores of less than 7 at 5 minutes and neonatal admission.
6. **Duration of the Project** We will recruit participants between February 2013 and June 2014.

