**D. Induction after Removal of Balloon**

For women who do not enter spontaneous labor during the ripening process, amniotomy will be performed once the catheter is expelled or removed. Women will be given intravenous oxytocin to induce the labor if the contraction was unsatisfactory after 30 minutes of amniotomy (<3 contractions per 10 min). Intravenous oxytocin will be started at an infusion rate of 1 mIU/min. The dose will be increased by 2 mIU/min every 20 minutes until adequate uterine activity is achieved, defined as uterine activity of 200-250 Montevideo units. The maximal infusion rate permitted is 25 mIU/min. Oxytocin will be discontinued once the women is deemed to be in active labor. If amniotomy is failed, the woman will receive oxytocin induction for 6 hours. Then the doctor will try amniotomy again.

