**7. Statistical Analysis**

Statistical analysis of outcomes data will be performed with SPSS 17.0. Data will be analyzed on an intention-to-treat basis. Normally distributed data will be presented as means with SDs; skewed distributions will be presented as medians with IQRs or medians with ranges. Categorical outcomes will be summarized using frequency distributions. For quantitative data, ANOVA or rank sum test will be used. For categorical data, we will calculate p values with Chi-square or Fisher exact tests. For time-to-delivery data, we will construct Kaplan-Meier survival curves and calculate log-rank test and p values. A probability value of 0.05 will be used as the cut-point for significance.

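### The allocation envelope is opened before catheter insertion although the arms differ only from inflation, so failed insertions dilute the comparison and cost power

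*Protocol*

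**What the plan says.** Protocol section 6.1 B places randomisation directly after consent: "After informed consent, the obstetrician and another investigator will open the envelope containing the assignment information".

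Section 6.1 C then describes the procedure, with no arm-specific step at the start: "Under direct visualization, a 16-F Foley catheter will be inserted into the endocervical canal". Balloon volume first matters at the next step: "Once the catheter is past the internal os, the catheter balloon will be inflated with sterile saline solution". The ripening limits cannot separate the arms until 12 hours have passed.

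The same section foresees that the catheter may not go in: "The following will be indications for early cessation of treatment: (1) failure to insert the Foley catheter". Staff are to "still collect outcome data from women who have stopped treatments".

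Section 7 sets the analysis population: "Data will be analyzed on an intention-to-treat basis". Section 3, item 4 sets the endpoint: "The primary outcome is vaginal delivery within 24 hours". The sample size in section 3, item 7 (126 per group, 28% against 48%) mentions no allowance for women who receive no balloon.

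**The concern.** The trial asks which balloon size and which time limit work better when a Foley catheter is used (section 2). A woman in whom the catheter cannot be placed tells us nothing about either. Because the envelope has already been opened, she still counts in one of the four arms, and intention-to-treat rightly keeps her there. Her outcome cannot depend on a volume or time limit she never received, so she pulls the arm rates toward each other.

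The allocation does not appear to be needed until inflation, so this loss is avoidable. At stake are some of the planned 80% power and an estimated difference smaller than the one among women who received a balloon.

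**Working it through.** **Inputs from the protocol (section 3, item 7).** Rates 28% and 48%; two-sided α = 5%; power 80%; 126 per group; four groups, so 4 × 126 = 504 women, which matches the centre targets in section 4 (296 + 4 × 52 = 504).

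**Inputs assumed.** The failed-insertion fraction f is not given; I use 1% to 10%, equal across arms. The rate q of vaginal delivery within 24 hours in these women is not given either; I use 28%, equal across arms, and then vary it from 10% to 48%.

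**Reproducing the planned size.** The protocol's formula is n = 2λ / h², with h = 2 arcsin √p_max − 2 arcsin √p_min.

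- h = 1.5308 − 1.1152 = 0.4156, so h² = 0.1727.
- λ is not defined in the text. Taking it as the noncentrality of a chi-square test on 3 degrees of freedom at 5% and 80% power gives λ = 10.903.
- n = 2 × 10.903 / 0.1727 = 126.25, which matches the stated 126. With 1 or 2 degrees of freedom the formula gives 91 or 112, so the plan is sized for the overall four-group test.
- At n = 126 the noncentrality is 126 × 0.1727 / 2 = 10.88 and the power is 79.9%.

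**Dilution.** With failed insertions kept in their arms, each arm's rate becomes (1 − f)p + fq. The largest difference is then (1 − f)(0.48 − 0.28), that is (1 − f) × 20 points, whatever q is. Example for f = 5%, q = 28%: 0.95 × 0.48 + 0.05 × 0.28 = 0.470 against 0.280; h = 0.3956; noncentrality 126 × 0.3956² / 2 = 9.86; power 75.4%.

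| f | failed insertions among 504 | difference (points) | power at 126 per arm, q = 28% | power, q from 10% to 48% | n per arm for 80%, q = 28% |
|---|---|---|---|---|---|
| 0 | 0 | 20.0 | 79.9% | 79.9% | 127 (126.25 before rounding) |
| 1% | 5 | 19.8 | 79.1% | 79.0–79.2% | 129 |
| 2% | 10 | 19.6 | 78.2% | 78.0–78.4% | 132 |
| 5% | 25 | 19.0 | 75.4% | 74.9–75.9% | 140 |
| 10% | 50 | 18.0 | 70.5% | 69.5–71.6% | 155 |

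The choice of q hardly matters; the result turns on f. For a single unadjusted comparison of 28% with 48% at 126 per arm, power is 91.0% without failures, about 88% at f = 5% and about 84–85% at f = 10%.

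**The case against.** Randomising straight after consent is ordinary practice and contradicts nothing else in the protocol. Outcome data are still collected after cessation and the analysis is by intention-to-treat, so the plan as written gives a valid comparison of induction policies. That stands: there is no inflation of type I error, and no bias for the policy question, if all randomised women are analysed.

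The size of the loss rests on an undocumented f. That also stands. At 1–2% the loss is negligible, and nothing in the protocol shows that 5–10% should be expected.

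The protocol nowhere says that one device serves both 30 and 80 mL; this is inferred from the single 16-F catheter and single technique. If the devices differ, size must be known before insertion and the change would not work as proposed. The order of envelope and insertion is likewise inferred, from the sequence of 6.1 B and C and from failed insertion being a cessation reason, but it is hard to read otherwise.

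The objection that later randomisation narrows the population is true but weak here, because the aim in section 2 concerns induction in which a Foley catheter is used.

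A reader might infer two stronger points.

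- That the intention-to-treat analysis will be broken by exclusions made by an operator who knows the arm. The protocol says the opposite: outcomes are collected after cessation and women are analysed as randomised.
- That these women have no start time for the 24-hour count. The protocol never ties that count to insertion. If induction begins with the attempt, they do have one. The undefined start affects every woman and is a separate issue.

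Two gaps for these women are side matters: section 6.1 D takes up care from the point where "amniotomy will be performed once the catheter is expelled or removed", and Appendix 2 has no box for failed insertion. Neither depends on when the envelope is opened.

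**Conclusion.** The point holds as an avoidable loss of efficiency. Opening the envelope before insertion turns each failed insertion into a randomised woman who received neither factor under study, and the planned difference shrinks to (1 − f) × 20 points. Four-group power falls from 79.9% to roughly 79%, 78%, 75% or 71% at assumed failure rates of 1%, 2%, 5% or 10%. These figures assume the same f and the same outcome rate in failed insertions in every arm, and λ taken on 3 degrees of freedom, which reproduces the stated 126. The documents do not support calling this bias or an error in the analysis. It is worth changing because the remedy is cheap, not because the present order invalidates the trial.

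**What to change.** In sections 6.1 B and C, have the second investigator open the envelope once the catheter is past the internal os and immediately before inflation, with both people confirming the allocation. First confirm, and state in 6.1 C, that the same catheter serves both volumes. Consent and the baseline Bishop score stay where they are. Log a woman in whom the catheter cannot be passed as consented but not randomised, and pass her unopened envelope to the next woman.

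Costs:

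- A few sentences in the protocol; no extra staff, since two people already open the envelope.
- The envelope is opened during the procedure.
- Results apply to women in whom a catheter can be placed, which fits section 2.
- Slightly more women must be consented to randomise 504: 504 / (1 − f), that is 515 at f = 2%, 531 at 5% and 560 at 10%.

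If the present order is kept, the alternative is to state an expected f and enlarge the arms: at q = 28%, 4 × 140 = 560 women at f = 5% or 4 × 155 = 620 at 10%. A box in Appendix 2 for a catheter that was not inserted, and one for cessation at the woman's or the obstetrician's request, would be useful but optional.

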**D. Induction after Removal of Balloon**

For women who do not enter spontaneous labor during the ripening process, amniotomy will be performed once the catheter is expelled or removed. Women will be given intravenous oxytocin to induce the labor if the contraction was unsatisfactory after 30 minutes of amniotomy (<3 contractions per 10 min). Intravenous oxytocin will be started at an infusion rate of 1 mIU/min. The dose will be increased by 2 mIU/min every 20 minutes until adequate uterine activity is achieved, defined as uterine activity of 200-250 Montevideo units. The maximal infusion rate permitted is 25 mIU/min. Oxytocin will be discontinued once the women is deemed to be in active labor. If amniotomy is failed, the woman will receive oxytocin induction for 6 hours. Then the doctor will try amniotomy again.

**E. Management of Labor**

When a woman is in active labor, maternal heart rate, blood pressure and temperature will be recorded every 6 hours, fetal heart rate and uterine activity will be continuously recorded with fetal heart monitor. The attending doctors will make clinical decision when there is an abnormal fetal heart tracing or failure to progress.

**F. Postpartum Management**

After delivery, participants will be managed according to postpartum routine of each center. Obstetricians will collect clinical information within 48 hours after discharge of the participants and complete *Case Report Form for Balloon Induction* (Appendix 2.). In addition, we will make telephone calls to every woman 30 days after delivery and record neonatal outcomes and late onset complications, such as puerperal infection and puerperal hemorrhage.

**G. Adverse Reactions**

Hyperstimulation is defined as more than 5 uterine contractions in 10 minutes in consecutive 30-minute intervals with or without fetal heart rate changes [9].

Failed induction is identified as failure to progress into the active phase of labor, despite adequate contraction patterns 24 hours after amniotomy.

Failure to progress is diagnosed as unchanged cervical dilation in a 4-hour interval, despite the establishment of well uterine contraction.

Chorioamnionits is diagnosed as maternal fever（≥38°C），accompanied by maternal tachycardia (>100bpm), or uterine fundal tenderness, or fetal tachycardia (>160bpm), or purulent amniotic fluid [10].

Postpartum hemorrhage is defined as blood loss of more than 500 mL within 24 hours of delivery. Blood loss is measured by: 1) collecting and recording of blood in bedpan containers; 2) weighing of materials including soaked sponges and pads on a scale and subtracting the known dry weights of these materials.

1. **Data collection for spontaneous labor**

**A. Recruitment and consent**

Women will be eligible as control group if they are nulliparous, singleton pregnancy in vertex presentation, less than 2 cm dilated at admission, and have spontaneous onset of labor. We will exclude women who deliver preterm, have fetus with congenital anomalies, or deliver by cesarean section. Participants need to sign written informed consent and clinical data will be used for research. Maternal age will be matched and difference of gestational age at delivery should be less than 7 days.

**B. Data collection**

Obstetricians will collect clinical information within 48 hours after discharge of the participants and complete *Case Report Form for Spontaneous Labor* (Appendix 3.). In addition, we will make telephone calls to every woman 30 days after delivery and record neonatal outcomes and late onset complications, such as puerperal infection and puerperal hemorrhage.

1. **Schedule**
2. Preparation phase (From June 2012 to Jan 2013)

In this phase, we have focused on preparations for the trial protocol and meeting with the coordinator of each center. Staff has been trained on Bishop scoring and Foley catheter balloon insertion. Oxytocin induction protocols has been designed and tested. Research protocol and management systems have been put in place.

1. Implementation of the trial (From Feb 2013 to Jun 2014)

Implementation of the randomized controlled trial will start. Pregnant women will be enrolled and followed up until 30 days postpartum. Once the target number of pregnancies has been enrolled, enrollment will be discontinued.

1. Analysis of data and report preparation (From Jul 2014 to Dec 2014)

Scientific papers, reports and presentations of the findings will be made.

**7. Statistical Analysis**

Statistical analysis of outcomes data will be performed with SPSS 17.0. Data will be analyzed on an intention-to-treat basis. Normally distributed data will be presented as means with SDs; skewed distributions will be presented as medians with IQRs or medians with ranges. Categorical outcomes will be summarized using frequency distributions. For quantitative data, ANOVA or rank sum test will be used. For categorical data, we will calculate p values with Chi-square or Fisher exact tests. For time-to-delivery data, we will construct Kaplan-Meier survival curves and calculate log-rank test and p values. A probability value of 0.05 will be used as the cut-point for significance.

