7. **Sample Size** Our previous study using an 80mL balloon with a maximum of 24 hours indicated a vaginal delivery rate in 24 hours of 28.1%[7]. A review of studies of various balloon sizes and ripening time showed a vaginal delivery rate within 24 hours ranges from 48% to 66%. Under this scenario, we assumed that by revising the Foley catheter induction protocol we could achieve a clinically significant increase in vaginal delivery within 24 hours. Thus planned sample size for this investigation was 126 patients each treatment group to show an increase in vaginal delivery rate within 24 hours from 28% to 48% with a two-sided test (α error=5%, power=80%). Formula: $n=2\lambda/{(2\sin^{-1} \sqrt{p_{max}}-2\sin^{-1} \sqrt{p_{min}})}^{2}$
8. **Labor patterns** To investigate the progress of labor in women induced with Foley catheter versus spontaneous labor, we will prospectively collect the information of women with spontaneous onset of labor and vaginal delivery in a 1:1 ratio in Nanjing Drum Tower Hospital. Women will be eligible as control group if they are nulliparous, singleton pregnancy in vertex presentation, less than 2 cm dilated at admission, and have spontaneous onset of labor. We will exclude women who deliver preterm, have fetus with congenital anomalies, or deliver by cesarean section. Participants need to sign written informed consent and clinical data will be used for research. Maternal age will be matched and difference of gestational age at delivery should be less than 7 days.

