**Appendix 2. Case Report Form for Balloon Induction**

| Year of Birth | (m/year) | | | Patient ID | | | |  |
| --- | --- | --- | --- | --- | --- | --- | --- | --- |
| Height | cm | | | Wt before Delivery | | | | Kg |
| GA | w d | | | G/P | | | |  |
| Indication | - □Prolonged gestation - □FGR - □Medical | | | - □GDM／DM   □Oligohydramnion | | | | - □PIH   □ICP  □Other |
| Group | □ 30mL Balloon×12h  □ 80mL Balloon×12h | | | □30mL Balloon×24h  □80mL Balloon×24h | | | |  |
| Time of induction |  | | | Bishop before induction | | | |  |
| Time of Removal |  | | | Bishop after induction | | | |  |
| Indication for | □Spontaneous | | | □Time limit reached | | | | □Abnormal CTG |
| Balloon Removal | □Hyperstimulation | | | □Rupture of membrane | | | | □Abnormal Bleeding |
|  | □Active labor | | | □Discomfort | | | |  |
| Induction after | □Amiotomy | | | Time | | | |  |
| Balloon Removal | □Oxy  □Max dose of Oxy | | | Time | | | |  |
|  | □Other | | | Time | | | |  |
| Labor patterns |  | | |  | | | |  |
| Time | | | Dilation of cervix | | | Decadence of presentation | | |
|  | | |  | | |  | | |
|  | | |  | | |  | | |
|  | | |  | | |  | | |
|  | | |  | | |  | | |
|  | | |  | | |  | | |
|  | | |  | | |  | | |
|  | | |  | | |  | | |
|  | | |  | | |  | | |
|  | | |  | | |  | | |
|  | | |  | | |  | | |
|  | | |  | | |  | | |
|  | | |  | | |  | | |
| Time of Delivery | |  | | |  | |  | |
| Mode of Delivery | | □Vaginal Spontaneous | | | □CS | | □Vaginal Instumental | |
| Indication for CS | | □Failed indution | | | □Abnoral Labor | | □Other | |
|  | | □Abnormal CTG | | | | | | |
| Indication for Assisted | | Vaginal Delivery | | |  | |  | |
| Analgesia | | □Epidural | | |  | |  | |
| PPH | | ml | | | Blood Transfusion | | □ Yes □No | |
| Maternal infection | | □No | | | □Chorioamnionitis | | □Endometritis | |
| Hyperstimulation | | □No □Yes | | | | |  | |
|  | | □ Uterus Rupture | | |  | | □ Placenta Abruption | |
| Other complications  Postpartum Diagnosis | |  | | | Postpartum Stay | | D | |
| Neonatal Birth Wt | |  | | | Apgar Score | | □1min 5min | |
| Neonatal Admission | | □Ward □NICU | | | □No | |  | |
| Indication | | □Infection | | | □Asphyxia | | □MAS | |
|  | | □RDS | | | □Low birth weight | | □HIE | |
|  | | □Other | | | □Neonatal Death | |  | |

Duration of Stay D

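### The primary test ignores the baseline Bishop score already being collected; adjusting for it would give a modest gain in power, though the planned test is valid

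*Protocol*

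**What the plan says.** Section 3, item 4: "The primary outcome is vaginal delivery within 24 hours". Section 7 assigns no test to this outcome by name. It gives one rule for all categorical outcomes: "For categorical data, we will calculate p values with Chi-square or Fisher exact tests". It names no model with covariates.

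The design has four arms: "Participants will be randomly allocated to one of four parallel groups, in 1:1:1:1 ratio". On size, item 7 of section 3 states that the "planned sample size for this investigation was 126 patients each treatment group", to detect a rise from 28% to 48% with a two-sided 5% test and 80% power.

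The Bishop score is determined during the eligibility assessment (section 6, Recruitment and consent), before the envelope is opened, and entry requires a score below 6 (section 3, item 3). It is listed on the checklist in Appendix 1 and has a field on the case report form in Appendix 2, "Bishop before induction". Gravidity and parity are on both forms.

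Parity is discussed only as a stratification factor: "Since 95% of women undergoing labor induction in our district are nulliparous, we will not stratify women according to parity". Section 3 names no other stratification factor.

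**The concern.** A baseline score that helps predict the outcome can be used to sharpen the comparison between randomised groups. Here the score is measured before allocation as part of eligibility, so it costs nothing more to collect. Randomisation does not stratify on it and the stated test does not use it. Whatever outcome variation it explains stays in the comparison as noise.

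The stake is power. The sample size formula leaves no margin at 126 per group, and the sample size paragraph states no allowance for dropout, so a few points of power from data in hand are worth having. Because section 7 states a method, this is a proposal to change that method. It is not a complaint about something left to an analysis plan.

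**Working it through.** **1. Reproduce the protocol's sample size.** The formula in section 3, item 7 is n = 2λ / (2·arcsin√p_max − 2·arcsin√p_min)².

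- With p_max = 0.48 and p_min = 0.28, the arcsine difference is 0.4156.
- λ for a chi-square test with 3 df, α = 0.05 and power 80% is 10.903.
- n = 2 × 10.903 / 0.4156² = 126.25, which matches the stated 126.
- With 1 df the same formula gives 91, and with 2 df it gives 112. The stated size therefore belongs to the unadjusted four-arm test.

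As a cross-check, assume rates of 28/38/38/48%. The noncentrality is 126 × (0.10² + 0.10²) / (0.38 × 0.62) = 10.70, and power is 79%. The planned test has about the power claimed for it.

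**2. What the Bishop score could explain.** The documents give no prognostic strength, so these inputs are assumptions: scores rounded and truncated to 0–5, mean 3, SD about 1 to 1.2, overall rate 38%, odds ratio (OR) 1.2 to 2.0 per point. The share of outcome variance explained is R² = Var(p) / (0.38 × 0.62). Adjustment acts roughly as if λ became λ/(1 − R²), with 3 df and a critical value of 7.815.

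| OR per point | R² | Approximate power at 126 per arm |
|---|---|---|
| none | 0 | 80% |
| 1.2 | about 1% | 80% |
| 1.4 | about 3% | 81% |
| 1.6 | 5–6% | 82–83% |
| 2.0 | 10–12% | 84–85% |

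**3. Direct simulation, Bishop score alone.** Settings: 126 per arm, rates 28/38/38/48%, SD 1.2, and 4,000 trials per row. The unadjusted chi-square is compared with a 3-df likelihood-ratio test from a logistic model containing group and Bishop score.

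| OR per point | Unadjusted | Adjusted | Gain (points) |
|---|---|---|---|
| 1.2 | 79.9% | 80.6% | 0.7 |
| 1.4 | 79.4% | 81.7% | 2.3 |
| 1.6 | 80.9% | 83.8% | 3.0 |
| 2.0 | 80.5% | 85.8% | 5.3 |

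The Monte Carlo standard error of each gain is 0.3 to 0.4 points. Allowing for that, the range is roughly 1 to 6 points. With no treatment effect, the unadjusted test rejected in 4.4–5.0% of trials and the adjusted test in 4.9–5.2%, so the gain is not bought with type I error. The weak end needs care. In a separate run (2,000 trials per setting) with no prognostic effect at all, the likelihood-ratio test still rejected slightly more often than the chi-square (81.3% v 80.6%). A gain below 1 point cannot be told apart from the change of test.

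**4. What parity could add.** At 5% parous, 0.05 × 504 ≈ 25 women, or about 6 per arm. R² = 0.05 × 0.95 × (difference in rates)² / (0.38 × 0.62). For assumed parity odds ratios of 2, 4, 6 and 8, R² is 0.6%, 2.2%, 3.4% and 4.3%. Multiplied by 126, that is worth about 1 to 5 women per arm.

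In the separate run, adjusting for both variables gave 80.4 v 81.4% (Bishop OR 1.2, parity OR 2), 78.2 v 80.7% (1.4, 4), 79.1 v 83.6% (1.6, 6) and 80.1 v 87.1% (2.0, 8). Only the strongest assumptions reach 7 points.

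**The case against.** The strongest reply is that nothing here is wrong. A chi-square test on a randomised binary outcome is valid, and chance imbalance in the Bishop score is already covered by its error rate. The 126 per group was derived for exactly this test. No passage says that the Bishop score strongly predicts delivery within 24 hours, and entry below 6 narrows its range and so limits what it can explain. Covariate adjustment is also often set in an analysis plan, which is not at hand.

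All of that stands, and it limits the point to efficiency. It does not remove the point: section 7 does fix an unadjusted method, and a pre-allocation score is available.

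Three stronger readings might be inferred, and the documents support none of them:

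- **The primary comparison is biased or underpowered.** It is neither. Type I error is held, and the stated 80% reproduces.
- **Leaving parity out is a serious loss.** The protocol's own 95% nulliparous figure shows otherwise, as step 4 quantifies.
- **Both variables are established strong predictors in this population.** The protocol gives no effect size for either, so every gain shown above is conditional on an assumption.

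**Conclusion.** The point holds as a modest, optional improvement. Adjusting the four-group comparison for baseline Bishop score would add roughly 1 to 6 points to a power of about 80%, if the odds ratio lies between 1.2 and 2.0 per point and scores are spread over 0–5 with an SD near 1 to 1.2. The direction is secure if the score is prognostic at all. The size is not known from the documents, and at the weak end it is negligible. The planned analysis remains valid and consistent with its sample size.

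**What to change.** In section 7, state that the primary four-group comparison (3 df) uses a logistic model with treatment group and baseline Bishop score as a continuous covariate. Define that score as the one from the eligibility assessment, before the envelope is opened. Report standardised (marginal) risk differences between groups with 95% confidence intervals, and keep the unadjusted chi-square as a sensitivity analysis.

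Parity and centre may be added as optional covariates but should be fixed in advance. Parity will be sparse, at about 6 parous women per arm, and four of the five centres contribute 52 women each, about 13 per arm.

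Treatment should stay as four groups. Replacing it with balloon-size and ripening-time main effects would change the hypothesis and the degrees of freedom that the sample size rests on, and would need its own justification.

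The cost is a short addition to section 7 and slightly more analysis work, with no new data, for a gain of uncertain size. Any separate analysis plan must say the same. Fixing the covariate in advance also prevents it from being chosen after results are seen in an open-label trial.
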